### Proposed Telecare Service

DSNs and peer supporters experienced in diabetes self management will systematically provide telephone support and advice to patients referred from primary care after a change in the patient's diabetes management (medication and/or lifestyle changes) recommended by their GP. It will be offered as an addition to routine care. The supporters will work to a protocol that includes a detailed enquiry into adherence to prescribed therapy, identification of problems, and brief negotiation in which realistic manageable goals for lifestyle change and overcoming barriers are agreed. The overarching aim of the telecare support is to reinforce the goals already established between health professional and patient.

The supporters will be recruited using a specification that sets out essential and desirable attributes established from stakeholder consultation and user group involvement. They will be trained using a 2-day programme developed by Warwick Diabetes Care. The programme is based on the theoretical background to successful behaviour change as described by Anderson and Funnell [20] and Rollnick et al [21] and practical counselling skills to enhance people's own decision making [22]. The programme includes training in empowerment, motivational interviewing, active listening skills, a brief psychological intervention that has been shown to be an effective strategy to increase readiness to change, assessing readiness to change, and the negotiation of agreed changes. Supporters will subsequently obtain an understanding of the factors that affect health behaviour, methods to assist others in altering these behaviours, and mastering the application of these techniques via telephone. Peer supporters, to further enhance their experience of patient support provision will attend a series of structured role-play sessions.

For patients in an intervention arm of the trial, the first telecare call will be made 3–5 days after referral from the patient's GP. The telecare supporter will tailor (and document) the frequency of subsequent calls to each patient's needs. The 'standard package' will be offering subsequent contact during the periods of days 7–10, 14–18, 28–35, 56–70, 120–150 but some patients will require more frequent contact while others may want less. Before completion of each call, the telecare supporter will negotiate the time of the next call. Supporters will routinely provide feedback on all calls to the research team via a standard form. However, if the telecare supporter feels more immediate contact is required, they will follow a formal feedback process to the GP; for peer supporters this will be a two stage process of referral to nurse and then, where appropriate GP. The reasons for such contact will be documented. Discussion with diabetes specialist nurses who had experience of telephone contact with patients suggested that the mean follow-up call length will be 5–10 minutes. Hence, on average each patient within the intervention groups will receive a total telecare intervention of about 45 minutes duration.

Patients in the control group will receive a single call from a researcher lasting approximately 10 minutes. This call will inform the patient that s/he is allocated to the routine care group, and that is the only phonecall s/he receives. The patient will be encouraged to follow the medical advice given to her/him by the GP/practice nurse.

#### Setting

The study is being undertaken within general practices within the West Midlands South Strategic Health Authority. This is a socio-economically and geographically diverse region in central England in which to test uptake and effectiveness of the intervention and trial methodology. In all, 40 practices have agreed to participate. Training was given to a practice nurse and general practitioner from each practice on how to manage patient recruitment, inclusion and exclusion criteria, consenting, maintaining subjects in the trial, collecting data etc.

### Setting up the telecare intervention

Twelve DSNs and nine peer supporters have been recruited using the DSN directory, Warwick Diabetes Care User Group and an email support group hosted by Trefoil Solutions to work as sessional telecare supporters for the study. In addition to interest in the study, they need to be willing to work flexible hours and be able to attend the training programme outlined above. The telecare supporters will receive monthly email or telephone supervision from their trainer to monitor workload, feasibility of the intervention, adequacy of training, and discuss specific patients presenting difficulties for the telecare supporter. A proportion of the telecare interactions will be tape-recorded. The tapes will be used to validate the data recorded during telecare interactions by the supporter, as a means to enhancing quality improvement of the intervention and for training purposes. Consent will be sought both before and after each taped interaction.

A trial centre will be established which supporters and patients can access throughout the duration of the study. Referral processes will be in place to respond to patient concerns. All patient record files will be kept under lock and key at the telecare centre and accessible only to the telecare service providers and the lead researchers. Wherever possible, anonymised patient data will be used. Confidentiality will be maintained and all provisions of the Data Protection Act will be followed.

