## Methods/Design

This study is an RCT of three arms:

i. Telecare service provided by diabetes specialist nurses

ii. Telecare service provided by peer supporters

iii. Control group receiving routine care only

Randomisation to control or intervention will be carried out at the patient level. Within the intervention group, patients will be randomly allocated to either a nurse or peer telephone supporter. To limit bias arising from patients' perception of their randomisation, all patients will receive at least one phone call. This should also ensure that the referring healthcare practitioners are as blinded as realistically possible. Patients will not be informed about whether they are in the intervention or control groups. The name, address, telephone number, access times, current treatment, details of any recent change in therapy (medication, diet, monitoring, and physical activity programme) related to diabetes, together with any provisos that were made, will be sent to the trial centre by the referring GP/nurse.

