#### Sample size

The sample size is based upon the primary outcome measure of self efficacy, measured using the DMSES and has been constructed to detect a difference in the primary outcomes of self efficacy perceptions and psychological adjustment. A sample of at least 300 patients (minimum 100 in each arm) has been constructed to detect a difference in self-efficacy scores with an effect size of 0.35, 80% power at a level of 5% significance level [25]. Allowing for an attrition rate of 25% from initial recruitment, we will require 125 subjects in each arm (i.e. 375 participants in total).

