### Trial Analysis

Data will be entered in SPSS. A random 20% of the data will be entered twice to check for discrepancies with the original data. Descriptive methods will be used to demonstrate the consistency of the three groups, describe participant characteristics, to compare the refusers with the study participants and report levels of participation and drop out. Comparison of nurse and peer supporter outcome data, experiences and feedback will be provided. Analysis of variance will be used to evaluate baseline characteristics of participants compared to non-participants, overall significance of improvement across outcome measures, and dropout versus maintainers. For each patient, change in physiological measures from start to 6 months will be calculated and analysed using t-test for matched groups for both intervention and control groups. The magnitude of change in both primary and secondary outcome measures will be estimated and the 95% confidence intervals given. *Formal Statistical Input*: A research fellow in medical statistics will provide statistical support and advice throughout the study.

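### The stated analyses and sample size make no allowance for clustering by telecare supporter (12 nurses, 9 peers), so telecare-arm standard errors are too small at any supporter ICC above zero

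*Protocol article*

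**What the plan says.** Under Methods/Design, the article sets individual randomisation: "Randomisation to control or intervention will be carried out at the patient level", and within the intervention group "patients will be randomly allocated to either a nurse or peer telephone supporter".

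The section on setting up the telecare intervention gives the number of people delivering it: "Twelve DSNs and nine peer supporters have been recruited". Under Proposed Telecare Service, "The telecare supporter will tailor (and document) the frequency of subsequent calls to each patient's needs", and "Before completion of each call, the telecare supporter will negotiate the time of the next call". The second statement implies that a patient normally stays with one supporter, but the article does not say so outright. The control arm differs in structure: "Patients in the control group will receive a single call from a researcher".

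The Sample size section rests on an "effect size of 0.35, 80% power at a level of 5% significance level", with at least 100 patients per arm, raised to 125 for 25% attrition. It mentions neither an ICC nor a design effect.

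Trial Analysis names analysis of variance for the overall significance of improvement, a matched t-test on the change in physiological measures to 6 months, and 95% confidence intervals for change in primary and secondary outcomes. It adds: "Comparison of nurse and peer supporter outcome data, experiences and feedback will be provided". No model is named for that last comparison, and no supporter term appears in any of the methods.

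**The concern.** The design is partially nested. Two arms are made up of small groups of patients who share a supporter; the third arm has no such groups. The intervention is person-to-person counselling, so supporters may differ in effectiveness, and outcomes of patients with the same supporter may then be correlated. An analysis that ignores this counts each telecare patient as a full independent observation and reports intervals that are too narrow.

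Comparing nurse and peer provision with routine care is the second stated aim, and a nurse–peer comparison is also planned. With only 21 supporters, a few strong or weak individuals could be read as an effect of supporter type. The third aim is to judge whether a full-scale trial is worthwhile, and an estimate of the supporter ICC would be directly useful for that.

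**Working it through.** **Does the sample size contain a hidden clustering allowance?** For independent patients and a standardised difference of 0.35 with 80% power:

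- One-sided 5%, one arm against another: 2 × (1.645 + 0.842)² / 0.35² = 101 per arm.
- Two-sided 5%, both telecare arms pooled against control (2:1): 1.5 × (1.960 + 0.842)² / 0.35² gives 97 controls and 194 telecare patients.
- Two-sided 5%, one arm against another: 2 × (1.960 + 0.842)² / 0.35² = 129 per arm.

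The stated 100 per arm agrees with the first two and not the third. Both matching calculations assume independence, so there is no room in the figure for a design effect.

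**Inputs for the clustering check**

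- Supporters: 12 nurses and 9 peers (Setting up the telecare intervention).
- Analysed per arm: 125 × 0.75 = 93.75, taken as 94 (Sample size).
- Patients per supporter: 94/12 = 7.83 (nurse) and 94/9 = 10.44 (peer), assuming equal caseloads, all supporters active and one supporter per patient.
- Supporter ICC: not given. Assumed range 0 to 0.05.

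**Formulas**

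- Design effect in a telecare arm: DE = 1 + (m − 1) × ICC. Control: DE = 1.
- Factor by which the unadjusted standard error of a contrast is too small: R = √((DE₁ + DE₂)/2).
- Actual two-sided error rate at nominal 5%: 2 × (1 − Φ(1.96/R)).
- Two-sided power at 0.35: Φ(0.35/√((DE₁ + DE₂)/94) − 1.96).

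At ICC 0.05, for example, nurse DE = 1 + 6.83 × 0.05 = 1.34 and peer DE = 1 + 9.44 × 0.05 = 1.47. For nurse versus peer, R = √((1.34 + 1.47)/2) = 1.19.

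**Results (R; error rate; power)**

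| ICC | Nurse vs control | Peer vs control | Nurse vs peer |
|---|---|---|---|
| 0 | 1.00; 5.0%; 67% | 1.00; 5.0%; 67% | 1.00; 5.0%; 67% |
| 0.01 | 1.02; 5.4%; 66% | 1.02; 5.6%; 65% | 1.04; 6.0%; 64% |
| 0.02 | 1.03; 5.8%; 64% | 1.05; 6.1%; 63% | 1.08; 6.9%; 60% |
| 0.05 | 1.08; 7.0%; 60% | 1.11; 7.8%; 58% | 1.19; 9.9%; 52% |

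The within-arm change is affected by a factor √DE. At ICC 0.05 this is √1.47 = 1.21 in the peer arm, slightly more than the 1.19 for nurse versus peer.

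**Cross-check.** A simulation of 20,000 trials per ICC, with 100 per arm and uneven caseloads, gave error rates at ICC 0.02 of 6.2%, 6.3% and 7.2% (nurse vs control, peer vs control, nurse vs peer). At ICC 0.05 they were 7.3%, 8.4% and 10.8%. The order is the same and the figures are slightly worse than in the table.

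**The case against.** The strongest reply is that this is one condensed paragraph of an article, that a statistician advises throughout, and that a supporter term is the kind of detail an analysis plan not shown here could add. That is fair as far as the model goes. It does not dispose of the point, because the article names methods that assume independence and a sample size that reproduces only under independence. A later plan could repair the analysis, but the sample size as stated would still carry no design effect.

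Second, supporter variation may be small. Supporters share a 2-day training, work to a protocol with a standard set of call windows, and receive monthly supervision. Call frequency is tailored to the patient's needs, which is variation between patients and not in itself between supporters. This stands: it is a reason to include low ICC values, where the effect is slight, but nothing in the article shows that the ICC is zero.

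Third, a reader might infer more than the text supports:

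- That a t-test is fixed for nurse versus peer. The only t-test is a within-arm matched test on physiological measures, and no method is named for nurse versus peer. The named method that can compare arms is the analysis of variance.
- That supporters have a free hand over call length and style. Only the tailoring of call frequency is stated.
- That one supporter per patient is laid down. It is implied; supporters are described as sessional, and caseloads are not given.
- That clustering explains the low power. The 67% starting point is below 80% at ICC 0, for reasons unrelated to clustering: a two-sided pairwise test needs 129 per arm, and 125 less 25% leaves about 94.

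**Conclusion.** The point holds. Followed as written, the stated analyses understate standard errors in the telecare arms at any supporter ICC above zero. Among comparisons between arms, nurse versus peer suffers most because both its arms are clustered.

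The size cannot be fixed from the document. It depends on an assumed ICC and on patients largely staying with one supporter. Over ICC 0 to 0.05, the upper ends are a 7.0% error rate for nurse versus control, 7.8% for peer versus control and 9.9% for nurse versus peer, and power at 0.35 falls from 67% to about 60%, 58% and 52% respectively. At ICC 0.01 the inflation is at most about one percentage point. The comparisons with routine care are moderately exposed; the nurse–peer comparison is the one to treat with most caution. The documents do not support the claim that the intervals will be seriously wrong, only that nothing in the stated plan guards against it.

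**What to change.** 1. Make sure the supporter is recorded for each telecare patient, including any change of supporter. The article does not list supporter identity among the call data.
2. Replace the plain analysis of variance with a baseline-adjusted, partially nested mixed model: a random supporter effect in the two telecare arms only, control patients unclustered, and small-sample degrees of freedom (about 19 for nurse versus peer, 21 supporters minus 2). Take all three pairwise contrasts, including nurse versus peer, from this model.
3. Report the estimated supporter ICC with its uncertainty.
4. State plainly that the sample size makes no allowance for supporter clustering.

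This costs analysis wording and one data item; design and recruitment do not change. The downside is slightly wider intervals and a variance component that will be imprecise with 9 to 12 supporters per arm.

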### Inclusion/Exclusion Criteria

The inclusion/exclusion criteria were initially set as:

#### Eligible patients

Patients who have had a recent HbA1c greater than 8.0% and been advised of the need to improve their glycaemic control, with or without a change in prescribed tablet based therapy.

#### Exclusions

Patients on insulin, lacking a telephone, and those with severe accompanying disorders (e.g. mentally ill; severe learning difficulties; severe hearing difficulties) or disorders judged by the GP as likely to interfere with outcome interpretation. Exclusions will *not *be made on the basis of anticipated patient co-operation, except where there are objective reasons for so doing.

10 months into the trial, the clinical threshold for inclusion was lowered in response to requests from GPs to allow patients with baseline HbA1c > 7.4% (as opposed to the previous criteria of HbA1c > 8%) to become eligible for telecare. This modification to the protocol is in line with the current NHS targets (new GMS contract target is 7.4%) and the manner in which practices are organising and delivering their care. The latest research evidence published in the American journal *Diabetes Care *also supports this change in eligibility criteria. In addition, the change was supported by research findings published by Young et al (2005) which reported significant improvement in HbA1c values as a result of telecare for patient with baseline HbA1c > 7% [23].

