**Methods/Design:**

In a 3-arm RCT, participants are allocated to either an intervention group with Telecare service provided by a Diabetes Specialist Nurse (DSN), an intervention group with service provided by a peer supporter (also living with diabetes), or a control group receiving routine care only. All supporters underwent a 2-day training in motivational interviewing, empowerment and active listening skills to provide telephone support over a period of up to 6 months to adults with poorly controlled type 2 diabetes who had been recommended a change in diabetes management (i.e. medication and/or lifestyle changes) by their general practitioner (GP). The primary outcome is self-efficacy; secondary outcomes include HbA1c, total and HDL cholesterol, blood pressure, body mass index, and adherence to treatment. 375 participants (125 in each arm) were sought from GP practices across West Midlands, to detect a difference in self-efficacy scores with an effect size of 0.35, 80% power, and 5% significance level. Adults living with type 2 diabetes, with an HbA1c > 8% and not taking insulin were initially eligible. A protocol change 10 months into the recruitment resulted in a change of eligibility by reducing HbA1c to > 7.4%. Several qualitative studies are being conducted alongside the main RCT to describe patient, telecare supporter and practice nurse experience of the trial.

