## Discussion

### The Value of the Research to Public Health and Patient Care

It is anticipated that the provision of motivational telecare support will enhance the self-management of patients with type 2 diabetes leading to improved clinical and psychological outcomes and reduction in the likelihood of diabetic complications. In addition to the improvement in individual patient care, the service could provide a cost effective adjunct to routine care, alleviating the resource pressures currently experienced within primary care and secondary care practice while establishing a successful and robust method of responding to the increasing prevalence of diabetes.

The project, in light of its focus upon self-management, peer involvement and telephone support has the potential to demonstrate an approach that is relevant to realising progress towards the achievement of the care targets in relation to not only diabetes, but a range of long term conditions. The intervention offers a valuable tool in dealing with the difficulties and complications of long term conditions, and as such might be applicable in a wide range of settings.

The main trial started in autumn 2004, shortly after the introduction of the new General Medical Services contract for general practice and the implementation of the Quality and Outcomes framework (QOF) [29]. The new GMS contract substantially increased the workload for general practitioners, making participation in research less attractive, and this has had an adverse impact on patient recruitment. However, the QOF targets resulted in considerably more data on diabetes care being routinely collected by GPs for the annual QOF reports, and at the same time the QOF introduce financial incentives to bring the patients' HbA1c levels below the 7.4% threshold through the more aggressive prescription of oral hypoglycaemic agents and insulin. Together, this resulted in slow participant recruitment for the trial, due to a reduction in the number of eligible patients. In response, the clinical threshold for trial inclusion was lowered to allow patients with baseline HbA1c > 7.4% (as opposed to the previous criteria of HbA1c > 8%) to become eligible for telecare, in line with the manner in which practices are organising and delivering their care. The change in protocol mid-way through the trial will have implications on the presentation of the consort diagram and the interpretation of the study's findings.

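### The HbA1c entry threshold fell from above 8% to above 7.4% during recruitment, but the stated test of HbA1c change neither contrasts the arms nor adjusts for baseline HbA1c

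*Protocol article*

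**What the plan says.** The first entry rule, under Eligible patients, was: "Patients who have had a recent HbA1c greater than 8.0% and been advised of the need to improve their glycaemic control". The Exclusions section then records the amendment: "10 months into the trial, the clinical threshold for inclusion was lowered in response to requests from GPs to allow patients with baseline HbA1c >" (now 7.4%). The abstract reports the same amendment: "A protocol change 10 months into the recruitment resulted in a change of eligibility by reducing HbA1c to > 7.4"%. The Exclusions section links the new threshold to NHS targets ("new GMS contract target is 7.4"%), so entry now begins at the care target itself.

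The Discussion comments on the consequence: "The change in protocol mid-way through the trial will have implications on the presentation of the consort diagram and the interpretation of the study's findings". It does not say how the change will be handled.

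HbA1c is not the primary outcome: "The primary outcome is self-efficacy; secondary outcomes include HbA1c, total and HDL cholesterol, blood pressure, body mass index, and adherence to treatment". Aim 3 nevertheless gives the clinical data a role, alongside the behavioural outcomes, in judging whether a full-scale RCT is worth doing.

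Trial Analysis names three relevant procedures:
- Each patient's 6-month change in physiological measures is tested by a matched t-test in the intervention and control groups.
- Analysis of variance is used for the overall significance of improvement.
- Analysis of variance is also used for those who declined: "Analysis of variance will be used to evaluate baseline characteristics of participants compared to non-participants".

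None of the three mentions baseline HbA1c as a covariate, or whether a patient was approached before or after the threshold change.

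**The concern.** Patients recruited after the change can start much closer to the 7.4% target. Someone entering at 7.5% is 0.1 point above it, whereas someone entering at 8.1%, just over the first threshold, is 0.7 above it. If telecare lowers HbA1c more in patients who start higher, the average effect depends on how many patients enter from the lower band. That number is set by recruitment timing, not by the intervention.

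A matched t-test within one arm cannot show this. It also mixes any telecare effect with what would have happened anyway, including regression to the mean in patients selected for a high value. The readers most affected are those planning a full-scale trial, who need to know which baseline range the HbA1c effect describes.

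A lesser point concerns participants versus refusers. If uptake differed before and after the change, a comparison combining both phases could show an HbA1c gap that reflects timing rather than who agrees to take part.

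**Working it through.** The article states no figure for the HbA1c effect, its variability or the phase split, so there is none to reproduce. Apart from the two thresholds, the 125 per arm and the 25% attrition, every input below is an assumption.

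**1. Is the between-arm comparison damaged?**

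Inputs to a simulated two-arm comparison:
- 94 evaluable per arm (125 × 0.75 = 93.75, from Sample size)
- source-population HbA1c with mean 7.4 and SD 1.3, baseline within-person SD 0.6, follow-up SD 0.9
- 30%, 50% or 70% of patients entering before the change; 3,000 trials per setting

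With no true effect, the between-arm test of change rejects in 4.5–5.5% of trials. Adjusted for baseline HbA1c and phase, it rejects in 4.6–5.5%. Type I error is intact.

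**2. How far can the mix move the average?**

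Average = p × (effect before) + (1 − p) × (effect after), where p is the share entering before the change. Take effects of 0.50 and 0.25 points:

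| p | Weighted average | Simulated, unadjusted |
|---|---|---|
| 30% | 0.3 × 0.50 + 0.7 × 0.25 = 0.325 | 0.325 |
| 50% | 0.5 × 0.50 + 0.5 × 0.25 = 0.375 | 0.377 |
| 70% | 0.7 × 0.50 + 0.3 × 0.25 = 0.425 | 0.422 |

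The estimate recovers the true average. Adjustment leaves it, and its standard error of about 0.155, almost unchanged.

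Halving the effect for everyone recruited after the change is a strong assumption, because many of them still start above 8%. Under three assumed HbA1c distributions, 25–34% of post-change entrants fall between 7.4% and 8%. With 30–70% of patients entering after the change, the lower band's share s of the whole trial is 0.30 × 0.25 = 7.5% to 0.70 × 0.34 = 23.8%. If only that band has the smaller effect, the average is 0.50 − 0.25s, that is 0.48 to 0.44.

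**3. What does the stated matched t-test show?**

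In the same simulation the control arm, with no intervention, changes by −0.22 to −0.25 points, and its matched t-test is significant in 52–61% of trials. This is regression to the mean and would occur with a single threshold too; the phase mix moves it by only about 0.03. It shows that the within-group test cannot stand in for a comparison of arms.

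**4. Participants versus refusers**

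Assume equal numbers approached in each phase, phase means m₁ and m₂, uptake r₁ and r₂, and no true difference within either phase:
- Participant mean = (r₁m₁ + r₂m₂)/(r₁ + r₂)
- Refuser mean = [(1 − r₁)m₁ + (1 − r₂)m₂]/(2 − r₁ − r₂)

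Equal uptake gives a gap of 0. Means of 9.2 and 8.75 with uptake of 30% and 40% give 8.94 against 8.99, a gap of 0.05. Means of 9.2 and 8.4 with uptake of 30% and 50% give 8.70 against 8.87, a gap of 0.17.

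**5. Precision of results by baseline band**

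With a standard error of 0.155 overall and similar residual variance in each band, the lower-band standard error is 0.155/√s. That is 0.57 at s = 7.5% and 0.32 at s = 23.8%, so 95% limits of about ±1.1 to ±0.6 points. For baseline above 8% it is 0.155/√(1 − s), 0.16 to 0.18, or about ±0.32 to ±0.35.

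**The case against.** The strongest reply is that a condensed article may leave covariates, subgroups and interactions to a fuller plan, and that nothing here says the two phases will be analysed as one. That is right about silence, and the absence of a phase term is not the point. What stands is that the article does name a test for physiological change, and that test has no place for an arm contrast or a baseline covariate. The analysis of variance for overall improvement could be read as comparing arms, but the text does not say so and names no covariate.

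It is also fair that HbA1c is secondary, that nothing here touches the self-efficacy result, and that Aim 3 weighs clinical patterns together with behavioural outcomes. These limit the importance of the point without removing it. The article also cites support for telecare benefit at baselines above 7%, so a smaller effect near the target is a possibility, not a documented fact.

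Four stronger readings are tempting, and the document does not support them:
- *The HbA1c result is an uninterpretable mixture.* Randomisation is by patient, so the rule change reached all arms alike and the difference is a valid average over those enrolled.
- *The refuser comparison is confounded.* It is distorted only if uptake differed between phases, and no uptake is given.
- *Recruitment conditions differed between phases.* The Discussion places the new contract before the trial began; only the threshold is documented as changing.
- *The reasons given conflict.* GP requests and the Discussion's account ("Together, this resulted in slow participant recruitment for the trial, due to a reduction in the number of eligible patients") are compatible.

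**Conclusion.** The point holds as a matter of effect heterogeneity and of which test is named, not of bias in the randomised comparison. The threshold was lowered to the care target ten months into recruitment, the article says interpretation is affected, and the one test it specifies for physiological change cannot show how.

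The size cannot be fixed from the article. Under the assumptions shown, the average HbA1c effect varies by about 0.10 points (0.325 to 0.425) if benefit halves for all later entrants, and by about 0.04 (0.44 to 0.48) if it halves only for baselines of 7.4–8%. It does not vary at all if benefit is unrelated to baseline. Any false participant–refuser gap is 0 with equal uptake and 0.05 to 0.17 points in the unequal cases tried. This is a worthwhile, low-cost improvement to a secondary analysis that informs Aim 3.

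**What to change.** - Replace the within-group tests as the basis for inference on HbA1c with a between-arm analysis of 6-month HbA1c, with baseline HbA1c as a covariate. A separate phase term is not needed once baseline is in the model.
- Report the arm difference with 95% confidence interval for baseline above 8% and for above 7.4% to 8%, and the arm-by-baseline-HbA1c interaction as a descriptive estimate with its interval.
- Show the CONSORT flow separately for before and after the threshold change.
- Where the date of approach is available, show the participant–refuser comparison by phase.

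The cost is wording and a few table rows. Baseline HbA1c is already collected before randomisation, and no change in sample size is needed. Two limits remain. The lower-band and interaction intervals will be wide, so they should be presented as description and not as tests. The article's list of data on refusers does not include the date of approach, so its availability must be confirmed first.
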